**Fig. 1 Fig1:**
[figure not shown]
Representative screenshot of the online registry (https://redcap.unifesp.br/), referring to the general data entry and the patient’s inclusion in the study. **A** Login and password that each center receives to begin the data entry. **B** Selection of the research arm. **C**, **D** An overview of the data used

A separate confidential record will be maintained with the identifying information—full name of the patient and legal guardian, date of birth, sex, ethnicity, identifying number of the participating center, local hospital record, and REDCap ID—to ensure that duplication of patients in the study does not occur.

In the preoperative survey, the following information will be collected (Table 1).

**Table 1 Tab1:** Information on preoperative variables

Variable	Definition/categories
Patient identification number	Unique patient code
Age	In years
Date of birth	dd/mm/yyyy
Date of diagnosis	Date of the initial exam (CT, MRI, or transfontanellar ultrasound) documenting posterior fossa tumor + hydrocephalus
Lesion topography	Main location (> 50% of volume): • 4th ventricle • Cerebellar hemisphere • Cerebellar vermis • Cerebellopontine angle • Brainstem
Tumor size	Largest axial diameter (mm)
Histological classification	Preoperative diagnosis (if available) + pathological confirmation (e.g., astrocytoma, ependymoma, medulloblastoma, ATRT)
Malignancy grade	WHO 2021 classification (adjusted after final pathology report)
Clinical signs/symptoms	Headache, vomiting, dizziness, gait disturbance, diplopia, facial palsy, choking, etc.
Leptomeningeal spread	Leptomeningeal thickening/enhancement on contrast-enhanced MRI
Hydrocephalus on imaging	Radiological criteria: • Increased Evans index • Temporal horn dilation (> 2 mm) • Ependymal transudation • Ballooning of the 3rd ventricle • “Beaten silver” appearance • Empty sella • Concavity of the 3rd ventricle floor
Type of initial intervention	ETV, EVD, VPS, or tumor resection + date of procedure

For each procedure chosen as a management strategy for hydrocephalus, its particularities will be considered (Table 2).

**Table 2 Tab2:** Information on the modalities chosen for the treatment of hydrocephalus secondary to posterior fossa tumor

Procedure	Specific variables
VPS	• Location of proximal catheter (frontal/occipital) • Type of valve (fixed, adjustable, flow-regulated) • Brand (national/imported) • Antibiotic impregnation (yes/no) • Distal catheter trimming (yes/no)
EVD	• Use (pre- or intraoperative) • Location of proximal catheter (frontal/occipital) • Brand (national/imported) • Antibiotic impregnation (yes/no) • Initial height of the system
ETV	• Type of endoscope (rigid/flexible) • Satisfactory stoma (opening of the 3rd ventricle and Liliequist membrane, visualization of the basilar artery) • Opening instrument (Fogarty 3F/4F/5F, scissors, biopsy forceps)
Tumor resection	• Surgical approach: midline suboccipital, retrosigmoid, or far-lateral • Without pre/intraoperative implantation of drainage devices

During postoperative follow-up, data will be collected regarding the occurrence of postoperative complications associated with the initial surgical procedure (if any) (Table 3).

**Table 3 Tab3:** Postoperative information on complications associated with the surgical procedure

Outcome	Definition/criteria	Classification
CSF leak	CSF leakage through the surgical wound (posterior fossa/ETV) • *Simple:* resolves spontaneously or with simple measures (pressure bandage, lumbar puncture, suture reinforcement) • *Clinically important:* continuous leakage, need for dural/skin re-approach or placement of EVD/VPS	Simple/important
Pseudomeningocele	Palpable, clinical, or radiological subdermal CSF collection • *Simple:* improves with puncture/bandaging • *Clinically important:* does not improve, causes significant discomfort, wound risk, or requires surgery/EVD/VPS	Simple/important
Surgical site infection	ANVISA 2017 criteria • *Superficial incisional:* up to 30 days, skin/subcutaneous tissue, criteria of purulent drainage, positive culture or clinical signs • *Deep incisional:* up to 30–90 days (with implants), involves fascia/muscle, criteria of drainage, abscess, dehiscence, fever/local signs	Superficial/deep
Meningitis/ventriculitis	ANVISA 2017 criteria. Positive CSF culture OR clinical signs (fever, headache, neck stiffness, irritability) + laboratory/imaging/microbiology changes	Present/absent
Brain/subdural/epidural abscess/encephalitis	ANVISA 2017 criteria. Positive culture, surgical, histopathological or radiological finding; neurological symptoms and positive microbiology	Present/absent
Hyponatremia	Na + < 135 mg/dL or below laboratory reference, requiring intervention (fluid restriction/NaCl)	Present/absent
Hypernatremia	Na + > 145 mg/dL or above laboratory reference, requiring intervention (DDAVP)	Present/absent
Subdural hygroma	CSF collection over the cerebral convexity, below the dura, on imaging	Present/absent
Intracranial hemorrhage	Positive imaging finding • *Simple:* no clinical repercussions, no surgery • *Clinically relevant:* neurological symptoms + need for surgery	Simple/relevant
CSF hypotension	Orthostatic headache, improvement when lying down + imaging findings (small ventricles, collections, venous engorgement)	Present/absent
Histological classification	WHO 2021 – Tumor malignancy grade	According to WHO
Extent of resection	• Total: no residual tumor • Near-total: < 1.5 cm^3^ • Subtotal: > 1.5 cm^3^	Total/near-total/subtotal
Adjuvant treatment	Record of start date (CT and/or RT)	Date
Reinterventions/additional exams	Need for additional exams or subsequent surgeries, with documentation of type, date, reason, and hospitalization time	Details
Death	Date and relation to hydrocephalus or tumor	Date
Tumor surgery date	When different from initial hydrocephalus treatment	Date
Time intervals	Between initial treatment, tumor surgery, and start of adjuvant therapy	Days/months
Failure of initial treatment	Need for new surgeries for hydrocephalus or related death	Time to failure
Ascending transtentorial herniation	Imaging evidence or neurological worsening after EVD	Present/absent
New tumor hemorrhage	New hemorrhagic focus after EVD/VPS/ETV (imaging or clinical)	Present/absent
Qualitative assessment of the operative field	0–10 scale for two aspects: • Neural relaxation (0 = no relaxation, transdural herniation; 10 = complete relaxation, adequate space for manipulation) • Cerebellar quality (0 = extremely friable/bleeding; 10 = not friable, not bleeding)	Score (0–10)
Cerebellar mutism/posterior fossa syndrome	Diagnosis when criteria A and B1 (mutism) are present, or, in the absence of B1, when A + B2 + C or D are fulfilled Criterion A: Acquired cerebellar lesion (e.g., postoperative or stroke) with symptoms in the following criteria, appearing up to 2 weeks after injury Criterion B: Speech/language deficits: •*B1 Mutism:* total inability to speak •*B2 Impaired language:* short phrases (single words or 2–3-word phrases), agrammatism, atypical rhythm (slow, scanning, ballistic) and/or anomia. Criterion C: Emotional/affective changes: irritability, emotional lability, or flat affect. Criterion D: Motor dysfunction: apraxia, ataxia, dysmetria, hypokinesia, or hemiparesis	Present/absent

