## Discussion

The discussion regarding the safest and most efficient drainage method, and when to perform it (before, during, after tumor resection, or whether to simply monitor hydrocephalus after resection without the need for perioperative diversion), remains controversial in the literature [16–19], since each method presents characteristic advantages and disadvantages that also depend on hospital infrastructure [7].

Several studies reported in the literature are restricted to a single center [3, 7, 8, 17–21], and most are limited by the small number of participants [22]. Thus, multicenter, prospective, and randomized studies in this area are necessary [9, 16, 22].

Described in 1923 by William Mixter [23], endoscopic third ventriculostomy provides the benefits of treating hydrocephalus at presentation and reducing its incidence after resection, in addition to avoiding the placement of drains and enabling tumor resection under low intracranial pressure conditions [3, 6].

Moreover, the procedure reduces intraoperative and late complications associated with EVD and VPS placement and promotes the “physiological” restoration of cerebrospinal fluid circulation [21]. However, it is a procedure that may be associated with complications such as hemorrhage, bradycardia, hemiparesis, memory dysfunction, diabetes insipidus, epilepsy, infection, and fistula [21].

Tamburrini G et al. [24], in a study conducted with 30 children, reported that factors such as extent of tumor resection, degree of hydrocephalus, histology, and tumor location were not associated with ETV success. Srinivasan et al. [8] recommended the procedure only in cases of symptomatic hydrocephalus and reported a higher failure rate associated with ependymoma.

VPS is one of the alternatives for the treatment of hydrocephalus [25]. However, it may present complications such as infection, ascites, visceral perforation, hemorrhage, and peritonitis [21], as well as other rarer complications such as device migration or extrusion [26].

Metastatic cell dissemination, such as in medulloblastoma, may occur through the VPS catheter [27–29]. In patients under 19 years of age with hydrocephalus secondary to posterior fossa tumor, ETV failure occurs earlier when compared to VPS, although cumulative failure is lower with ETV (21%) than with VPS (29%) [30].

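### The two intracranial hemorrhage grades in Table 3 are not exhaustive: a bleed with neurological symptoms but no need for surgery, or the reverse, has no valid grade

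*Protocol article*

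**What the plan says.** The intracranial hemorrhage row of Table 3 (protocol article, Outcome assessment) has one entry condition, "Positive imaging finding". It then splits the bleeds into two grades:

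- *Simple*: "no clinical repercussions, no surgery".
- *Clinically relevant*: "neurological symptoms + need for surgery".

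The classification column lists the permitted values as "Simple/relevant", with no intermediate or other level. The Methods name mortality, infection and further complications of clinical relevance as the secondary outcomes.

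**The concern.** A two-level grade works only if every eligible event falls into exactly one level. Here the upper level needs two conditions together and the lower level needs both to be absent. A bleed that meets just one condition fits neither definition.

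The case that matters most is a hemorrhage that produces a deficit but is not judged to need an operation. Read as written, it cannot reach the serious category. A center would have to leave the grade empty or pick one whose definition is not met, and more than 20 centers could resolve this differently. The grade would then partly reflect local habit in judging which bleeds need surgery. The study compares four strategies chosen by the treating team, and covariate adjustment or propensity scores cannot repair an outcome that was graded differently by site.

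**Working it through.** The plan gives no figure on this point, so the check is one of logic and of how the table uses its own symbols.

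**Step 1: does the plus sign mean 'and'?** Two other rows of Table 3 settle this. The cerebellar mutism row applies "when A + B2 + C or D are fulfilled", which keeps the plus sign and 'or' distinct. The CSF hypotension row reads "Orthostatic headache, improvement when lying down + imaging findings", where the imaging is required in addition to the headache. The plus sign is therefore conjunctive.

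**Step 2: enumerate the combinations.** Let S = neurological symptoms from the bleed (yes/no) and N = need for surgery (yes/no). I treat the two grades as using the same S and N, although the simple grade words them slightly differently.

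- Simple = (not S) and (not N)
- Clinically relevant = S and N

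| S | N | Simple? | Clinically relevant? | Grade as written | Grade if S or N |
|---|---|---|---|---|---|
| no | no | yes | no | Simple | Simple |
| yes | yes | no | yes | Clinically relevant | Clinically relevant |
| yes | no | no | no | none | Clinically relevant |
| no | yes | no | no | none | Clinically relevant |

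As written: 1 simple + 1 clinically relevant + 2 ungraded = 4. With 'or': 1 simple + 3 clinically relevant + 0 ungraded = 4. If death from the hemorrhage is added as a third yes/no item, there are 2 × 2 × 2 = 8 combinations: 1 simple (none present), 8 − 1 = 7 clinically relevant, 0 ungraded.

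**Step 3: compare the neighbouring rows.** The severe grades of CSF leak and pseudomeningocele are lists of alternatives joined by 'or'. For a pseudomeningocele, marked discomfort alone is enough. The hemorrhage row is the exception: a neurological deficit alone is not enough.

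**Step 4: does another row supply the missing grade?**

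- New tumor hemorrhage is recorded as present or absent, with no severity, and concerns bleeding in the tumor.
- Reinterventions and additional exams records type, date and reason. It would show an operation for a bleed but would not grade the bleed.
- Death is recorded with its date and its relation to hydrocephalus or tumor; hemorrhage is not named as a cause.

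None of these assigns a severity grade to a bleed that meets only one condition.

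**The case against.** Several points on the other side are sound, and they limit the finding.

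- **Fatal bleeds.** A reader might infer that a child who dies of an unoperated hemorrhage always drops out of the serious grade. The text does not support that. The criterion is need for surgery, not surgery performed, so a symptomatic bleed judged to need an operation that never took place can still qualify. Deaths also have their own row, and mortality is a separate secondary outcome. What can be lost is the hemorrhage grade where surgery was not indicated, not the death.
- **Events are not lost.** Every imaging-positive bleed enters the row whatever its grade. An analysis of any hemorrhage would be unaffected.
- **Link to the secondary outcome.** The article does not say that the analysed endpoint is the two-level grade, or that only bleeds in the upper grade count. The shared label makes this a natural reading, but it remains an inference.
- **Size and direction.** A reader might infer a large undercount of serious bleeds, or that strategies whose bleeds are rarely operable will look safer. The article gives no hemorrhage rate, no share of bleeds needing surgery and no comparison of operability by group. The Discussion's list of ETV problems, "complications such as hemorrhage, bradycardia, hemiparesis, memory dysfunction, diabetes insipidus, epilepsy, infection, and fistula", is background from cited literature. It names hemorrhage and hemiparesis as separate items and compares no groups.
- **Condensed reporting.** The data-entry screens are not shown, so how the form behaves for a bleed between the grades is unknown. This does not cure the printed rule: the article states the definition and its permitted values in full, and that definition has a gap.
- **Pseudomeningocele.** Its simple grade is worded "improves with puncture/bandaging", so a collection that resolves untreated is not literally covered. Such a collection meets none of the severe criteria either, so no serious event is hidden. It is a matter of wording, not part of this point.

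**Conclusion.** The concern holds in limited form. Two of the four symptom-by-surgery combinations have no grade, and a bleed causing a deficit without need for surgery cannot be recorded as clinically relevant under the definition as printed. This is a stated rule that fails, not a detail left to a fuller document.

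The figure of two in four counts definitional cells, not patients; how many children would fall into them cannot be derived from the article. The conclusion rests on reading the plus sign as 'and', which the table's own usage supports. If 'or' was meant, the text still needs correcting. The effect is confined to the severity grade of one complication; the primary outcome and the sample size are untouched. The change should be made because it is specific and almost free, but the article does not support a claim of biased comparison between the four groups.

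**What to change.** Reword the hemorrhage row of Table 3 and the matching data-entry field:

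- *Clinically relevant*: neurological symptoms attributable to the hemorrhage, OR need for surgery, OR death from the hemorrhage.
- *Simple*: an imaging finding with none of these.

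Record the components as separate yes/no items and derive the grade from them, so that sites do not choose it. This changes how an outcome is classified, not how patients are managed.

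The cost is one or two extra fields and a somewhat higher count of clinically relevant hemorrhages than the present wording would give. As an optional alignment, the simple pseudomeningocele grade could also allow spontaneous resolution, as the CSF leak row already does.

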**Methods:**

This is a prospective, multicenter cohort study conducted across more than 20 pediatric neurosurgery centers in Latin America. Patients will be allocated into four groups according to the treatment selected for hydrocephalus (ETV, EVD, VPS, or resection). The primary outcome will be the number of surgical interventions related to the treatment of hydrocephalus during the follow-up period. Secondary outcomes will include mortality, infection, and other clinically relevant complications, analyzed as complementary endpoints. Patients will be followed prospectively for up to 12 months after the index procedure, defined as the intervention performed for the treatment of hydrocephalus, and each group will include at least 50 patients.

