## Methods

A prospective, multicenter, controlled cohort study will be conducted. The primary outcome will be the number of surgical interventions related to the treatment of hydrocephalus during the follow-up period, as it directly reflects treatment failure and holds significant clinical relevance. Secondary outcomes will include mortality, infection, and other clinically relevant complications, which will be analyzed as complementary endpoints. The study was approved by the Scientific Committee of the Instituto de Oncologia Pediátrica (IOP/GRAACC) and by the Ethics Committee of the Universidade Federal de São Paulo (UNIFESP), as well as by the ethics committees of all participating centers. Patients will be included in the study after obtaining written informed consent from their legal guardians and assent from patients under 18 years of age diagnosed with hydrocephalus secondary to posterior fossa tumors, confirmed by imaging studies (computed tomography (CT) and magnetic resonance imaging (MRI)), and who will undergo surgical resection of the posterior fossa lesion.

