### Outcome assessment

The primary outcome of this study will be the number of reintervention surgeries for the treatment of hydrocephalus after the index surgery for hydrocephalus treatment, which will be chosen at the discretion of each participating center and the attending physician responsible for the patient’s initial treatment.

Patients will be included after signing the Informed Consent Form and/or Assent Form and meeting the inclusion and exclusion criteria. Their data will be anonymously entered into the REDCap software (Fig. 1) for prospective follow-up. Each participating center will be recognized by a specific identifying number. Once the patient is selected to participate in the study, they will be prospectively followed, and each outcome event may be recorded in real time or at the predetermined follow-up times of 1 month postoperatively, 3 months, 6 months, 9 months, and 12 months, always considering day zero as the day on which the hydrocephalus treatment was performed.

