## Sample size calculation

The sample size calculation was performed considering the number of surgeries as the primary outcome, which is the main variable of interest in this clinical study. The primary analytical objective is to compare the effect of four treatment strategies on this outcome, with adjustment for age as a relevant covariate.

For sample size estimation, G*Power software version 3.1.9.6 [11] was used, as described by Kang [12], adopting the *F*-test family, specifically the ANCOVA option: fixed effects, main effects, and interactions, in an a priori analysis. This approach is widely used for comparisons between groups with adjustment for covariates in clinical studies [13–15]. A medium effect size (*f* = 0.25), a significance level of 5% (*α* = 0.05), and a statistical power of 80% (1 − *β* = 0.80) were assumed, as recommended to ensure adequate ability to detect clinically relevant differences. The model included four comparison groups and one covariate (age). Based on these parameters, a minimum total sample size of 179 participants was estimated. Assuming a 10% loss to follow-up, the total sample size would be approximately 200 participants, corresponding to about 50 individuals per group, resulting in a test with degrees of freedom *F*(3,174) and a statistical power of approximately 80%.

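### The primary count takes no account of death or shortened follow-up, while Table 3 counts a hydrocephalus-related death as treatment failure

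*Protocol article*

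**What the plan says.** The Methods section makes the primary outcome the "number of surgical interventions related to the treatment of hydrocephalus during the follow-up period, as it directly reflects treatment failure". Outcome assessment words it as the "number of reintervention surgeries for the treatment of hydrocephalus after the index surgery for hydrocephalus treatment". The abstract sets the window: "Patients will be followed prospectively for up to 12 months after the index procedure".

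Statistical analysis compares the primary outcome by ANCOVA. Sample size calculation names four groups and one covariate, age. No rate, person-time or censoring enters the primary comparison. The same section says: "Assuming a 10% loss to follow-up, the total sample size would be approximately 200 participants". It does not mention death.

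Death appears in three other places:
- Methods: "Secondary outcomes will include mortality, infection, and other clinically relevant complications, which will be analyzed as complementary endpoints".
- Table 3, row on death: "Date and relation to hydrocephalus or tumor".
- Table 3, row on failure of initial treatment: "Need for new surgeries for hydrocephalus or related death", classified as time to failure.

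**The concern.** The count is chosen because it is held to reflect treatment failure, but the article's only definition of failure includes an event that the count cannot register. A child who dies of hydrocephalus before a second operation has no reinterventions. Under the Outcome assessment wording the value is zero. If the broader Methods wording is read to include the index operation, the value is still the minimum. In Table 3 the same child has failed.

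Tumour deaths and losses raise no conflict with Table 3, but they also shorten the time in which a reintervention can be counted. If mortality differs between arms, the raw mean shifts in favour of the arm with more early deaths.

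Equal early mortality is not a safe default. Treatment is chosen by the centre and physician, and the Discussion concedes selection bias. Day zero is the hydrocephalus procedure. In the resection arm that is the tumour operation itself. In the other arms the tumour operation may come later, and consent may follow the drainage procedure, so a child recruited afterwards has already survived it.

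**Working it through.** **1. The plan's own figure.** ANCOVA with f = 0.25, α = 0.05, 4 groups, 1 covariate: df1 = 3, df2 = N − 5, λ = 0.25² × N. The smallest N with power of at least 0.80 is 179 (df 3 and 174, power 0.801). 179/0.9 = 198.9, so about 200. Both figures reproduce. The point concerns the outcome, not this arithmetic.

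**2. One child under both definitions.**

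| Course within 12 months | Primary count | Table 3 failure |
|---|---|---|
| Alive, no reoperation | 0 | no |
| Alive, one reoperation | 1 | yes |
| Hydrocephalus-related death, no reoperation | 0 | yes |
| Tumour death, no reoperation | 0 | no |

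The third row is the conflict. The fourth shows shortened time at risk without a conflict.

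**3. Size of the shift in the mean.** Assumptions, none from the article: 0.5 reinterventions per child-year in every arm; 12-month mortality q of 15% in one arm and 5% in another.
- Every death before any reoperation: mean = 0.5 × (1 − q). This gives 0.5 × 0.85 = 0.425 and 0.5 × 0.95 = 0.475. Ratio 0.895, an apparent advantage of about 11% for the arm with more deaths. This is the upper limit.
- Constant death hazard: mean time at risk = q / (−ln(1 − q)). This is 0.15/0.1625 = 0.923 and 0.05/0.0513 = 0.975 years, so the means are 0.461 and 0.487. Ratio 0.947, about 5%.
- Constant death hazard, with half of reinterventions in the first two months and half spread over the other ten: mean survival over those two periods is 0.987 and 0.910 at 15% mortality, 0.996 and 0.971 at 5%. The averages are 0.948 and 0.983. Ratio 0.965, about 3.5%.

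**4. Effect on the F test.** Simulation of Poisson counts, 50 per group, 4,000 runs, the same true rate in every arm (0.3 to 1.0 per child-year), one-way F test without the age covariate, nominal level 5%:

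| 12-month mortality | Deaths spread over the year | All deaths at 1 month |
|---|---|---|
| 10% in all arms | about 5% | about 5% |
| 5% in three arms, 20% in one | about 5–6% | 6–10% |
| 5% in three arms, 30% in one | 6–8% | 9–19% |

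**5. Does a log-time offset cure it?** Assume 70% of reinterventions fall in the first two months, mortality 20% against 0%, constant death hazard. Mean survival over the first two months is 0.982 and over the rest 0.879. The raw count ratio is 0.7 × 0.982 + 0.3 × 0.879 = 0.951. Mean time at risk is 0.2/0.2231 = 0.896. The offset rate ratio is 0.951/0.896 = 1.06. The raw count is about 5% too low and the offset rate about 6% too high, so the offset reverses the bias.

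**The case against.** The best reply has four parts.

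**Silence is not a rule.** A reader might infer that the plan scores early deaths as zero by rule, places deaths in the 10% loss, or drops partly followed children. The article says none of this. The zero is a consequence of the definition, and how incomplete follow-up is handled may be set out in the analysis plan that the Discussion mentions and that is not shown. That stands, and those readings are not claimed here. What remains is that the article itself fixes a raw count, calls it a direct reflection of failure, and defines failure elsewhere to include related death.

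**Different endpoints may treat death differently, and death is not ignored.** Mortality is a secondary outcome, its date and cause are recorded, and time to failure is collected. This is true, so it would be wrong to say that the study overlooks death. It does not cure the primary comparison, which is offered as the measure of failure and does not say how it is to be read with the others. The Table 3 conflict is confined to hydrocephalus-related deaths before any reoperation; the sizes above use all-cause mortality and so measure the shortened follow-up, not that conflict alone.

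**Follow-up is common by design.** Visits run to 12 months from day zero for every child, so only death or loss shortens it. Agreed.

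**The effect is small.** Even one arm at 0.425 and three at 0.475, with an SD of about 0.7, give f = 0.0217/0.7 = 0.03 against the planned 0.25. At N = 200 the F test would reject about 6% of the time instead of 5%. This stands for moderate mortality differences. It weakens when deaths are early and very unequal (9–19% in the extreme case above).

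**Conclusion.** The point holds in a limited form. The primary count and Table 3 rank a hydrocephalus-related death before reoperation in opposite directions, and the count falls with any early death or loss. The direction is unfavourable, since more early deaths make a strategy look better. The size is uncertain because the article gives neither mortality nor reintervention rates by arm. Under 15% against 5% mortality and equal reintervention rates, the apparent advantage is about 5% with deaths spread over the year and at most about 11%. With low and equal mortality it is negligible. The 11% should not be read as the expected bias, nor the finding as showing that the primary test is invalid. The change is still worth making, because the study seeks the most appropriate strategy and the remedy is cheap.

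**What to change.** 1. Make Table 3's composite the key supporting analysis, reported beside the primary count: time from day zero to first hydrocephalus reintervention or hydrocephalus-related death, with other deaths as competing events and loss to follow-up censored.
2. State in advance that no strategy is called better on the count alone if this analysis or mortality points the other way.
3. Keep partly followed children by estimating the 12-month mean cumulative number of reinterventions, with loss censored and death as a terminal event. This deals with loss only. If nobody is lost it equals the raw mean, so it does not replace step 1.
4. Use a count model with a log-time offset only as a sensitivity analysis, because it assumes a constant rate and treats death as ordinary censoring.

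Dates of reintervention and death and the relation of death to hydrocephalus are already in Table 3. The planned ANCOVA and the figure of 179 can stay as they are. The cost is a few sentences, one or two more analyses, and a primary result that is no longer read alone.

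### Three Table 3 complications (ascending herniation, CSF leak, deep incisional infection) are counted on terms that depend on the index procedure, so comparing them between arms is distorted by ascertainment; separately, the sodium unit is wrong

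*Protocol article*

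**What the plan says.** The Methods section makes infection and other clinically relevant complications secondary outcomes. The Introduction and Discussion state the aim of comparing four strategies (ETV, EVD, VPS, resection), and the Statistical analysis section assigns multivariable regression to secondary outcomes. Table 3 gives the definitions:

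- Ascending transtentorial herniation: "Imaging evidence or neurological worsening after EVD".
- CSF leak: "CSF leakage through the surgical wound (posterior fossa/ETV"). EVD and VPS wounds are not listed.
- Surgical site infection, under ANVISA 2017 criteria. Superficial: "up to 30 days, skin/subcutaneous tissue". Deep: "up to 30–90 days (with implants), involves fascia/muscle".
- New tumor hemorrhage: "New hemorrhagic focus after EVD/VPS/ETV (imaging or clinical").
- Hyponatremia: "Na + < 135 mg/dL or below laboratory reference", and needing intervention. Hypernatremia: "Na + > 145 mg/dL or above laboratory reference", and needing intervention.

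Table 2 describes the resection arm as having no drainage device placed before or during the operation. The Methods and eligibility sections require every patient to undergo posterior fossa resection.

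**The concern.** A between-arm comparison of a complication needs the event to be countable on the same terms in every arm. If the definition changes with the index procedure, arms with identical true risk will show different recorded rates. Covariate adjustment and propensity methods deal with differences in who receives each treatment. They do nothing about events that one arm may record and another may not. Nor can a later analysis recover events that were never entered in REDCap.

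The rows bear on questions the study wants to answer: infection is a named secondary outcome, and the Discussion itself treats the link between EVD and CSF leakage as disputed.

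**Working it through.** **The plan's own figure.** The only calculated figure in the article is the sample size, which does not depend on Table 3. With a noncentral F test, f = 0.25, α = 0.05, four groups and one covariate (df1 = 3, df2 = N − 5, noncentrality = f²N), the smallest N with power of at least 0.80 is 179 (df2 = 174, power 0.801). Then 179/0.90 = 198.9, so 199, against the stated approximately 200. It reproduces.

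The article gives no complication rates. Every event rate below is therefore an assumption, shown as a range, with 50 patients per arm.

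**Herniation.** The row can be read in two ways.

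- Reading A: the reference to EVD governs the whole row. Only EVD patients can have the event.
- Reading B: it governs only the clinical part. Imaging evidence counts in every arm, and EVD alone also qualifies on clinical worsening without imaging.

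Both readings favour recording in the EVD arm. Reading B cannot be sized, because the frequency of the extra route is unknown. Under reading A with equal true risk r in all arms, the recorded EVD count is binomial(50, r) and all other counts are 0. Fisher's exact test reaches p < 0.05 with at least 3 EVD events against 0/150, or at least 6 against 0/50.

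| Assumed r | Expected EVD events | False rejection, EVD vs other 150 | False rejection, EVD vs one arm of 50 |
|---|---|---|---|
| 2% | 1 | 8% | 0.05% |
| 5% | 2.5 | 46% | 4% |
| 10% | 5 | 89% | 38% |

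**CSF leak.** Let a be the leak risk at the posterior fossa wound (all arms) and b the leak risk at the access wound, assumed equal for ETV, EVD and VPS. ETV records 1 − (1 − a)(1 − b); EVD and VPS record only a.

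| a | b | Recorded, ETV | Recorded, EVD or VPS | Spurious ratio |
|---|---|---|---|---|
| 5% | 2% | 6.9% | 5% | 1.38 |
| 10% | 5% | 14.5% | 10% | 1.45 |
| 15% | 10% | 23.5% | 15% | 1.57 |
| 10% | 10% | 19.0% | 10% | 1.90 |

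**Deep incisional infection.** Let s be the share of infections by day 90 that fall on days 31 to 90. At equal true risk, the recorded ratio of implant to no implant is 1/(1 − s): 1.11 for s = 10%, 1.33 for s = 25%, 1.67 for s = 40%.

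**Sodium.** With a molar mass of 22.99 g/mol (a physical constant, not in the article), 135 mg/dL × 10/22.99 = 58.7 mmol/L and 145 mg/dL × 10/22.99 = 63.1 mmol/L. Conversely, 135 and 145 mmol/L equal 310 and 333 mg/dL. The printed numbers and the printed unit do not belong together.

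**The case against.** Several points on the other side are sound and limit the finding.

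- **Herniation.** A reader might infer that the count is zero by construction in three arms. That holds only under reading A, and the text does not settle which reading is meant. What survives is that EVD has the wider definition either way.
- **CSF leak.** A reader might infer that EVD and VPS patients cannot have a recorded leak. They can, at the posterior fossa wound. A leak elsewhere that leads to surgery would also appear in the reinterventions row with type, date and reason. Even so, it would not count as a CSF leak under that row's definition, and milder leaks would not be captured.
- **Deep infection.** A reader might infer a threefold excess from 90 against 30 days. That needs a constant hazard to day 90, which nothing in the article supports. Nor are some children followed longer: all have visits to 12 months, and only the counting window differs. The rule depends on implants rather than on named arms, so a patient shunted later would also carry an implant. Whether a temporary EVD counts as an implant is not stated. Superficial infection, meningitis/ventriculitis and abscess have no implant-dependent window in the table. The window still largely follows arm, and attributing it to a surveillance standard does not make unequal windows comparable.
- **New tumor hemorrhage.** A reader might count this as a fourth faulty row. It is not one: in the resection arm the index procedure is the tumor resection, so limiting the row to the three diversion arms makes sense, and a separate intracranial hemorrhage row covers all arms.
- **Scope.** Table 3 is a data-collection table, and the article does not say that every row will be contrasted across four arms. Infection and complications are nevertheless secondary outcomes of a comparative study.

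**Conclusion.** The point holds for three secondary outcomes. Ascending herniation, CSF leak and deep incisional infection are defined in ways that depend on the index procedure, and their between-arm comparison would be distorted by what is recorded. Other rows, such as pseudomeningocele, meningitis/ventriculitis, hygroma and intracranial hemorrhage, use neutral wording, so neutral definitions are feasible.

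The size cannot be fixed from the article. The ratios of 1.38 to 1.90 for leak and 1.11 to 1.67 for deep infection, and the false rejection rates for herniation, rest on assumed event rates; the herniation figures also rest on the narrower reading of that row. The primary outcome and sample size do not use these definitions.

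The sodium unit is a separate, plain error. A reader might infer that it biases the comparison, or that nobody meets the lower limit and everybody exceeds the upper one. Neither follows: the error is the same in every arm, and each row also accepts the local laboratory reference and requires that an intervention was needed.

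**What to change.** Edit Table 3 and the matching REDCap fields:

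1. Record ascending herniation after any index procedure, under one criterion applied identically in all arms.
2. Record CSF leak from any operative, drain or shunt wound, with the site as its own field.
3. For the between-arm comparison, count deep incisional infection over one common window in every arm: 90 days, with the same starting rule, using the existing 1- and 3-month visits. Record implant status as a field, and tabulate the ANVISA definition separately.
4. State that new tumor hemorrhage is compared only among the three diversion arms.
5. Replace mg/dL in both sodium rows with the unit in which 135 and 145 are meant.

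The cost is minor: a few form edits and a little extra data entry at visits that already exist. The sample size does not change.
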